#### Economic evaluation

The proposed intervention may have economic implications through two mechanisms. First, there may be differential personnel and administrative costs related to the IPT program itself. Second, pilot data suggest that the intervention may lead to decreased use of healthcare resources [130]. The objective of the economic analysis will be to estimate the cost-effectiveness of the addition of telephone-based IPT compared to standard postpartum care of mothers with PPD. In order to facilitate comparison with other healthcare programs, the analysis will take a societal perspective, in which consideration will be given to all costs regardless of the parties to whom they accrue. Thus, direct medical costs will be supplemented by data on volunteer labor costs, medical and non-medical costs borne by the mother herself or her family, and mother or family time absent from work. Cost data will also be presented in a disaggregated format to improve the generalizability of the results to parties having other perspectives, such as the provincial ministry of health or community organizations.

#### Comparators and time horizon

The alternatives in the trial are telephone IPT vs. standard postpartum care of mothers with PPD. Given that IPT in this context is adjunctive, the economic analysis will retain a high degree of external validity. The economic component of the study will measure costs from randomization to 36 weeks post-randomization. We recognize that the resource implications of the trial intervention will probably extend beyond that point. As the incidence of affective symptoms gradually decreases, however, the longer-term cost differences between programs are also likely to decrease. Moreover, the costs of implementing the intervention itself will be fully captured. The measured cost-effectiveness will therefore be a conservative estimate. Decision analytic modeling of longer-term outcomes beyond 36 weeks will be undertaken in secondary analyses if there are still differences between groups in resource utilization and costs at the end of trial data collection.

#### Analytic technique

Results will be approached using incremental cost-effectiveness analysis, in which the additional costs and effects for the IPT will be compared to the costs and effects of standard community postpartum care for mothers with PPD. All analyses will be performed on an intention-to-treat basis.

#### Measurement of resource utilization

We anticipate that resource use will consist of the following factors: (1) direct medical costs, including (a) fees for healthcare professionals (b) hospital care, (c) drug prescriptions (anti-depressant medication); (2) direct non-medical costs, including (a) travel costs incurred by patients to obtain care, (b) child care expenses; (3) productivity losses due to patient and family work absence; and (4) cost to administer the IPT intervention including (a) recruiting and training nurses, (b) nurses’ time for providing IPT, and (c) IPT supervision.

Resource use will be ascertained through activity logs completed by the IPT nurses. For the use of professional healthcare services, participants will complete a slightly modified version of the self-report Health Service Utilization and Costs of Care Questionnaire [128]. The latter questionnaire also includes items for direct non-medical costs and work absence.

#### Valuation of unit costs

Physician fees will be derived from local provincial fee schedules [147] and average hourly wages for registered nurses will be applied. Price weights for hospitalization episodes will be obtained using aggregate data from standardized hospital cost accounting systems in British Columbia and Alberta and from the Ontario Case Cost Project of the Ministry of Health Joint Policy and Planning Committee [148]. Total costs per patient will be the summed products of quantities of resources used multiplied by these unit prices. Given that the time horizon for the measured outcomes included in the current study protocol is short, discounting of costs and effects will not be undertaken for the primary analysis.

#### Determination of effects

Efficacy will be expressed as the recovery of PPD at 12 weeks post-randomization (immediately post-treatment for mothers in the intervention group), as dictated by the primary outcome of the trial. Secondary cost-effectiveness ratios consistent with the trial’s secondary endpoints will also be reported. Given the relatively standardized nature of the intervention and the acute setting, compliance is anticipated to be good. Furthermore, the study population is not very restrictive, with the only excluded patients being those already receiving pharmacological or psychotherapeutic intervention, those with a current or past bipolar diagnosis, and/or those with chronic depression or suicidal ideation, most of whom would not avail themselves of the intervention outside of the trial context. It is likely therefore that the economic evaluation will have very good external validity; no adjustments to approximate real-world effectiveness are planned.

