There are more than 500 reports of published studies using the SCID-I as a diagnostic instrument and the reliability and validity has been extensively reported in diverse studies and samples [112]. In particular, research evaluating the SCID-I has found the measure to yield highly reliable diagnoses for most disorders [112,113], with inter-rater reliability often exceeding 81 % for diagnoses such as major depression [114]. The SCID-I has also been effectively used with postpartum women to assess depression [115-120]. The SCID training materials, for both clinicians and research personnel, include a user’s guide and eight videotapes. At the UCLA Research Center for Major Mental Illnesses, a training and quality assurance program was used to evaluate SCID inter-rater reliability and diagnostic accuracy. Both clinically experienced interviewers and recently trained neophyte interviewers were able to achieve and maintain high levels of inter-rater reliability, diagnostic accuracy, and interviewer skill; at the first quality assurance check after training, there were no significant differences between experienced and neophyte interviewers in inter-rater reliability or diagnostic accuracy [121].

The SCID-I is also administered at 24 and 36 weeks post-randomization, as a secondary outcome. While some attrition of the sample is expected by this time, the additional information will provide important evidence of longer-term effects of the IPT intervention.

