### Operational details

#### Telephone-IPT intervention

Mothers allocated to the treatment group receive 12 weekly IPT sessions, each session 50 to 60 min in duration and delivered over the telephone by a trained IPT nurse who receives weekly supervision by an IPT trainer ([name]). Within 72 h, the IPT nurse will either administer session 1 (if possible) or at least make an initial call to the participant to schedule session 1 (to occur within the week following enrolment). The scheduling of IPT sessions are based on mutual availability between the mother and IPT nurse. IPT is administered according to the standardized manual by Stuart and Robertson [56,140], with some modifications to accommodate the postpartum context of depression. These modifications are based on previous IPT trials for PPD [141].

As conducted in standard IPT clinical practice, a minority of trial participants identified as either in acute crisis at the end of treatment, or who are progressing however remain significantly symptomatic, thus would benefit from extending the course, may be offered up to four additional IPT sessions (that is, conduct 12 or a maximum of 16 sessions per trial participant, as appropriate). A full course of therapy must be completed within 16 weeks to account for any additional sessions and/or occasional scheduling conflicts or difficulties.

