#### Uncertainty and statistical issues

Uncertainty will be assessed through sensitivity analysis for non-stochastic inputs such as choice of price weights. For stochastic variables including efficacy and costs, a non-parametric bootstrap method will be used to generate joint confidence intervals for the cost-effectiveness ratio. This technique involves resampling, with replacement, of the observed distribution of costs and effects, to establish an empirical distribution of cost-effectiveness ratios, from which confidence intervals can be constructed. Sample size will be determined by statistical consideration for the detection of efficacy in the clinical trial. In the absence of information regarding the dependence of costs and effects, it is problematic to determine power for comparisons of cost-effectiveness ratios a priori. The economic evaluation will therefore take an estimation, rather than hypothesis testing, approach to the construction of incremental cost-effectiveness ratios. Cost-effectiveness ratios and 95 % confidence intervals will be estimated using non-parametric bootstrapping [149]. The frequency with which these intervals overlap with cost-effectiveness thresholds of $0 to $300,000 per PPD recovery will be reported using cost-effectiveness acceptability curves.

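### The acceptability curve is defined by ratio intervals overlapping thresholds, which is not an acceptability curve, and the main ratio sets 36-week costs against 12-week recovery

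*Protocol article*

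**What the plan says.** All references are to the economic part of the protocol article.

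- **Costs.** Under Comparators and time horizon: "The economic component of the study will measure costs from randomization to 36 weeks post-randomization". The same section argues that the intervention's cost will be fully captured and that later cost differences should shrink, and concludes: "The measured cost-effectiveness will therefore be a conservative estimate".
- **Effect.** Under Determination of effects: "Efficacy will be expressed as the recovery of PPD at 12 weeks post-randomization". The reason given is that this is the trial's primary outcome. The section adds: "Secondary cost-effectiveness ratios consistent with the trial’s secondary endpoints will also be reported".
- **Uncertainty.** Under Uncertainty and statistical issues, costs and effects are resampled with replacement "to establish an empirical distribution of cost-effectiveness ratios, from which confidence intervals can be constructed". The quantity to be shown as an acceptability curve is then "The frequency with which these intervals overlap with cost-effectiveness thresholds" between $0 and $300,000 per PPD recovery.
- **Later diagnoses.** Under Postpartum depression: "The SCID-I is also administered at 24 and 36 weeks post-randomization, as a secondary outcome". Table 1 also lists the cost questionnaire at 12, 24 and 36 weeks.

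**The concern.** Two stated rules looked wrong.

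The first is the curve. An acceptability curve gives, for each amount a payer might spend per recovery, the probability that the intervention is worth that amount. Whether an interval for the ratio overlaps the amount is a different question. It can give a no both where the intervention is almost certainly too dear and where it is almost certainly good value. Ratios also cannot be put in a meaningful order once the effect difference changes sign: a negative ratio may mean better and cheaper, or worse and dearer.

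The second is the horizon. Care used between weeks 12 and 36 enters the numerator. Relapse among treated mothers and late recovery among controls in those weeks do not enter the denominator. The argument for calling the result conservative concerns costs. It does not consider whether the effect lasts from week 12 to week 36.

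At stake is whether the reported cost per recovery and the curve answer the value-for-money question they are presented as answering.

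**Working it through.** **1. The plan's own figure.** The economic section states no computed figure. The denominator of its main ratio is the effect on which the trial is sized: 70% against 50% depressed at 12 weeks, two-sided 0.05, 80% power (Justification for sample size). With pooled variance and no continuity correction:

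n = [1.960·√(2·0.60·0.40) + 0.842·√(0.70·0.30 + 0.50·0.50)]² / 0.20² = (1.358 + 0.571)² / 0.04 ≈ 93 per group.

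The article states 94, so this reproduces to within one. 188/0.80 = 235, so 240 covers a 20% loss. The sample size is not in dispute.

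**2. Share of replicates with a negative effect difference.** After 20% loss, 240 × 0.80 / 2 = 96 per arm remain. The standard error of the difference is √((0.21 + 0.25)/96) = 0.069, and the share is Φ(−d/0.069).

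| True difference d | Share negative |
|---|---|
| 20 points (planned) | 0.2% |
| 10 points (assumed) | 7% |
| 5 points (assumed) | 24% |

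The variance is held at the 70%/50% value throughout. With 70%/65% for the 5-point row, the standard error is √((0.21 + 0.2275)/96) = 0.0675 and the share is about 23%.

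**3. Overlap against acceptability.** The documents give no costs, so these are assumed: incremental cost $1,500, cost SD $4,000, costs independent of recovery. The run used 96 per arm, 5,000 bootstrap resamples and a 95% percentile interval for the ratio. Whole-patient rounding makes the nominal 20- and 10-point effects 19/96 and 9/96. Acceptability at threshold λ is the share of replicates with λ·ΔE − ΔC > 0.

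| Threshold | 20 points: in interval? | 20 points: acceptability | 10 points: in interval? | 10 points: acceptability |
|---|---|---|---|---|
| $0 | no | 0.006 | yes | 0.003 |
| $2,500 | yes | 0.06 | yes | 0.02 |
| $20,000 | yes | 0.94 | yes | 0.59 |
| $50,000 | no | 0.99 | yes | 0.81 |
| $100,000 | no | 0.996 | yes | 0.87 |

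The intervals are about $1,300 to $28,500 (20 points) and about −$84,000 to $108,000 (10 points). With 20 points, overlap gives the same answer, no, at acceptability 0.006 and at 0.99. With 10 points it is yes at every threshold tried from $0 to $100,000 and discriminates nothing. With no effect and the same cost, 0.51 of the ratios fall below $0 while acceptability at $0 is 0.005, which shows the mixing of signs.

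**4. Horizon.** For a fixed, positive 36-week incremental cost ΔC, the ratio on 36-week recovery divided by the ratio on 12-week recovery is (ΔC/d₃₆)/(ΔC/d₁₂) = d₁₂/d₃₆. With d₁₂ = 20 points:

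- d₃₆ = 20 points: 20/20 = 1, no change.
- d₃₆ = 10 points (assumed): 20/10 = 2.
- d₃₆ = 5 points (assumed): 20/5 = 4.
- d₃₆ above 20 points: below 1, so the 12-week ratio overstates.

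Nothing in the article fixes d₃₆ or ΔC.

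**The case against.** The strongest defence has four parts.

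- **The curve is a slip of wording.** The section names acceptability curves, plans joint resampling of costs and effects, and gives a threshold range, which is all that a standard curve needs. Because one interval has no frequency, the author may well have meant a frequency across replicates. This stands as a likely intention. The written rule nevertheless names intervals and overlap, and an analyst following it would not produce the curve.
- **Percentile intervals are not specified.** This is correct: the article says only that intervals can be constructed from the distribution of ratios. A reader might infer that the planned interval is invalid as it stands. The documents do not support that, because at the planned 20-point effect only about 0.2% of replicates are negative. The problem arises with smaller effects, which could include those behind the secondary ratios.
- **The horizon is partly handled.** The secondary ratios can include recovery at 36 weeks against 36-week costs. This stands. What remains is that the main ratio is mismatched, that no matched ratio is named, and that the mismatch is not discussed.
- **The stakes are limited.** Cost is among the other research questions, the approach is estimation, and health-unit budgets have a separate analysis based on personnel costs. This also stands.

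**Conclusion.** The point holds as a minor one. The definition of the curve is wrong as written, whatever the costs turn out to be. The ordering problem for ratio intervals is negligible at the planned effect, and matters only if the effect is nearer 10 or 5 points, both of which are assumed here.

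The main ratio has mismatched horizons and equals a matched one only if the 12-week difference persists to 36 weeks, so the description as conservative is not assured. A reader might infer that it understates the cost per recovery two- to fourfold. The documents do not support that. Those multiples need the effect to shrink to a half or a quarter and the incremental cost to be positive. The article reports maintained effects in small uncontrolled group-IPT studies (Background) and pilot data pointing to lower resource use (Economic evaluation). Neither the size nor the direction of the distortion can be derived. The primary clinical analysis does not depend on any of this.

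**What to change.** 1. **Curve.** Replace the overlap sentence. In each joint patient-level bootstrap replicate, compute incremental net benefit (threshold × effect difference − cost difference). Plot the proportion of replicates with net benefit above zero at each threshold from $0 to $300,000 per recovery. Report a confidence interval for net benefit alongside the ratio.
2. **Horizon.** Make recovery on the SCID-I at 36 weeks against 36-week costs the main ratio, or an explicitly named co-reported one. Keep the 12-week recovery ratio, labelled as having mismatched horizons, and drop or qualify the claim that it is conservative.
3. **What to avoid.** Do not match horizons by cutting costs at 12 weeks. The article allows sessions after that point ("A full course of therapy must be completed within 16 weeks"), so intervention costs would be lost. If depression-free weeks are added as a further analysis, they need their own threshold scale, because the stated range is per recovery, and they need interpolation between visits.

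The cost is a few sentences and a few lines of code, with no new data. One downside is that 36-week diagnoses will have more missing values than 12-week ones, though costs to 36 weeks already depend on the same follow-up.

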#### Budgetary impact analysis

In addition to the preceding efficiency analysis, the budgetary impact at the participating health regions will be explored. In this analysis, the total personnel costs for each of the health units will be compared, assuming that health units either persist with standard postpartum care for mother with PPD or alternatively adopt the telephone-based IPT program. This analysis will assume that the care of new mothers with PPD had costs and outcomes of either the intervention or control group. The analysis will be repeated under several assumptions regarding the size of the program, the percentage of depressed mothers identified, and the percent of a nursing full-time equivalent required to provide and maintain the IPT program.

#### Uncertainty and statistical issues

Uncertainty will be assessed through sensitivity analysis for non-stochastic inputs such as choice of price weights. For stochastic variables including efficacy and costs, a non-parametric bootstrap method will be used to generate joint confidence intervals for the cost-effectiveness ratio. This technique involves resampling, with replacement, of the observed distribution of costs and effects, to establish an empirical distribution of cost-effectiveness ratios, from which confidence intervals can be constructed. Sample size will be determined by statistical consideration for the detection of efficacy in the clinical trial. In the absence of information regarding the dependence of costs and effects, it is problematic to determine power for comparisons of cost-effectiveness ratios a priori. The economic evaluation will therefore take an estimation, rather than hypothesis testing, approach to the construction of incremental cost-effectiveness ratios. Cost-effectiveness ratios and 95 % confidence intervals will be estimated using non-parametric bootstrapping [149]. The frequency with which these intervals overlap with cost-effectiveness thresholds of $0 to $300,000 per PPD recovery will be reported using cost-effectiveness acceptability curves.

#### Exploratory analyses

Exploratory analyses will be performed using data collected in the entire sample to explore relationships among the SCID and other study outcomes.

#### Predefined subgroups

None.

### Trial status

Recruitment is ongoing with 212 participants enrolled as of March 9, 2012.

## Abbreviations

BDI Beck: Depression inventory; CES-D: Centre for epidemiologic studies depression scale; DAS: Dyadic adjustment scale; DSM-IV: Diagnostic and statistical manual of mental disorders; ECR: Experiences in close relationships; ECR-R: Experiences in close relationships - revised; EPDS: Edinburgh postnatal depression scale; HRSD: Hamilton rating scale for depression; IPT: Interpersonal psychotherapy; MDE: Major depressive episode; PPD: Postpartum depression; SCID-I: Structured clinical interview for dsm axis i and ii disorders; STAI-State: Spielberger state-anxiety inventory.
